**Fig. 1 Fig1:**
[figure not shown]
Flow diagram of participant allocation

The parent program of the FBMI was designed by the Principal Investigator by means of some adaptations to two overseas mindful parenting programs [34, 35]. The program lasts for 6 weeks, and each session lasts 1.5 h. Each parent program can accommodate 15 to 20 parents. A protocol was prepared by the first author, and the session themes and key contents are summarized in Table 1. The parent programs are implemented by instructors employed by the research team or social workers from the three NGOs who have completed training organized by the Principal Investigator. All parent group instructors completed an 8-week mindfulness-based stress reduction program or mindfulness-based cognitive therapy program. Additional training was provided by [name], the trainer of another mindful parenting program [35], or the first author.

**Table 1 Tab1:** Child program of Family-based Mindfulness Intervention (developed by Snel, 2014)

Session	Theme	Goal
1	A for attention	- Establish motivation of be attentive and mindful
		- Use breathing as a beginning of exploration of attention
2	Exploring our body	- Introduce mindful movement exercises
		- Expand awareness of body sensation
3	Tasting, Smelling, Hearing, Seeing and Feeling	- Introduce the use of multiple senses in understanding our inner and outside world
4	Feel our feelings	- Learn to be aware and to describe feelings
5	Accepting feelings	- Acknowledge feelings of self and others
		- Experience the importance of accepting feelings
6	Conscious movement	- Bring attention and awareness to self and others
7	The power of awareness and thoughts	- Experience the application of mindful attention and thoughts in daily life
8	Being nice is good	- Consolidate learning
		- Practice of lovingkindness

For the child program, FBMI follows the child mindfulness program “Mindfulness Matters” (the green book for children 5 to 8 years of age) [36]. The program includes four to six children, and each session lasts 1 h. All group instructors possess a professional degree in social work, education, or clinical psychology and have been certified as instructors by completing the 6-day “Mindfulness Matters” professional training program.

During the fourth and sixth sessions of the parent program, 30-min joint activities are included. This design helps the family members to practice mindfulness together and to review their learning and progress in each other’s presence. The session themes of the child program are shown in Table 2. Participants in the wait-list group will receive the same intervention after the families from intervention group complete FBMI. The research team estimated that the study would be conducted in five cycles, with each cycle consisting of 24 families randomized into an intervention group and a waitlist control group.

**Table 2 Tab2:** Mindfulness training for parents (developed by the [name])

Session	Theme	Goal
1	Stress of being a parent	- Establish motivation to learn mindfulness for promotion of family health
		- Introduce mindfulness training
		- Introduce body scan
2	Automatic reactions	- Introduce stretching
		- Notice physiological, emotional and cognitive reaction in stressful moments of parenting
		- Use of mindful breathing and nonjudgmental attitude in managing the reaction in parenting
3	Respond to children mindfully	- introduce mindfulness to breath and body
		- Further notice reactive patterns in parenting
		- Introduce three minute breathing as coping
		- Practice deep listening in mindfulness
4	Quality parenting	- Joint session: practice with children, progress review
		- Introduce mindfulness to sounds and thoughts
		- mindful living for ADHD children and family caregivers
5	Facing difficulties with kindness	- Exploring difficulties with mindfulness practice
		- Introduce lovingkindness practice for self-care, and care of others
6	Self-care of parents	- Joint session: practice with children, progress review
		- Care plan of children and self
		- Consolidate learning

All parent and child groups are audio recorded. Among six parent group sessions or eight child group sessions, one session will be randomly selected the teaching integrity and performance. Parent group instructors will be evaluated using Mindfulness-Based Intervention–Teaching Assessment Criteria [37], while child group instructors will be evaluated by a 10 item evaluation constructed by the research team. Independent assessors are recruited by the research team and internal consistency and interrater reliability will be calculated. The child group evaluation form includes two areas, adherence to session protocol, and competence in program delivery. Assessor will give a rating from 1 to 5, in terms of the levels of adherence and competence, in each item of the scale.

All parents attended a screening interview. The full schedule of enrollment, interventions and assessments is included in Fig. 2. A research team member explained the procedure and research design to them in details. Once the parents agreed to participate in the study with their children, they were invited to sign on the consent forms before the study commenced.

**Fig. 2 Fig2:**
[figure not shown]
Schedule of enrollment, interventions and assessments

The study protocol has been reviewed by the funder of this study, the Health Care and Promotion Fund from the Food and Health Bureau, The Government of the Hong Kong Special Administrative Region. The study has been given ethical approval from the Research and Contracts Office of the City University of Hong Kong (ref. 3-3-201504_03) and is registered under the Chinese Clinical Trial Registry (ref. ChiCTR-IOR-15007292).

### Study sample

One hundred twenty children between 5 and 7 years of age with ADHD or with symptoms of inattention and hyperactivity and their parents are being recruited to participate in the FBMI. During the screening interview, all outcome measures and demographic information are completed by the parents. The inclusion criteria include (1) children age between 5 and 7 years and (2) a score that meets or exceeds the borderline cutoff of the Strengths and Weaknesses of ADHD Symptoms and Normal Behaviors Rating Scale (SWAN) [38]. The exclusion criteria include (1) children with another developmental disability, such as an intellectual disability or autism spectrum disorder, and (2) the inability of either the parent or the child to attend 80 % of the program sessions.

The randomization procedure is as follows. A 10 × 10 table was created by randomly assigning digits 0 to 9. One row of the table is randomly selected, and the sequence of digits in that row is observed. A participant list is prepared, and the sequence of participants is observed. The first digit will determine the first participant’s group, and so on. Participants with an even digit are assigned to the intervention group, and those with an odd digit are assigned to the control group. After the families are assigned to groups, another research team member contacts the parents by phone, to inform the parent about the results of randomization and to confirm that both the parent and the child will participate in the study. It means that team member who interviews the families is blinded in the assignment process.

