### Estimation of sample size

Because no studies of FBMI have been performed in the families of young children with ADHD, and because the effect sizes of studies of psychosocial treatments vary, the research team adopted an estimated effect size of 0.6 for changes in child attention and behavior. Based on a one-sided type I error of 5 % and 80 % power to detect statistically significant differences between the FBMI and wait-list control groups, the required sample size per arm is 45. Considering an attrition rate of 15 %, more than one hundred six families should be recruited for the study.

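### The stated randomization rule supplies 10 allocations, but each cycle randomizes 24 families, so 14 of 24 have no stated allocation

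*Protocol article*

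**What the plan says.** The randomization procedure is in the protocol article under Study sample, as a sequence of steps.

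- The source of digits: "A 10 × 10 table was created by randomly assigning digits 0 to 9".
- The draw: "One row of the table is randomly selected, and the sequence of digits in that row is observed".
- The link to families, after a participant list has been prepared: "The first digit will determine the first participant’s group, and so on".
- The allocation: "Participants with an even digit are assigned to the intervention group, and those with an odd digit are assigned to the control group".

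The number to be randomized is given in two places. Under Study design overview, just before Table 2, the team gives its estimate: "the study would be conducted in five cycles, with each cycle consisting of 24 families randomized into an intervention group and a waitlist control group". Study sample opens with the total: "One hundred twenty children between 5 and 7 years of age".

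The article does not say what happens after the tenth listed participant. It mentions no blocking or other balancing rule, and it does not say that the order of the participant list is fixed before the row is drawn.

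**The concern.** The two sections do not fit together. A rule that draws one row and uses one digit per participant stops at the tenth family, while each cycle puts 24 families through randomization. Someone must have decided, or will have to decide, how the other 14 get an arm, and the article does not say how.

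The comparison of the intervention with the waitlist rests on random allocation, so a reader needs to know that every family was randomized. Here that can be confirmed from the text for at most 10 families of a cycle. What is at stake depends on how the gap was filled. Some ways keep allocation random, and one obvious way does not.

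**Working it through.** **Inputs.** Table of 10 × 10 digits, one row drawn, one digit per family, even or odd decides the arm (Study sample). 24 families per cycle, five cycles (Study design overview). 120 families (Study sample).

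**The plan's own total.** 5 × 24 = 120. The two recruitment figures agree with each other.

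**Capacity of the rule.**
- One row gives 10 digits for 24 families: 10/24 = 42% covered, 14/24 = 58% not covered.
- One row in each of five cycles gives 5 × 10 = 50 digits for 120 families.
- The whole table gives 10 × 10 = 100 digits for 120 families, so even reading on through every row leaves 20 families without a digit.

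This much follows from the text alone. The rest is by scenario, because the text does not say what was done.

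**Scenario A: the same row is read again.** Families 11–20 copy families 1–10, and families 21–24 copy families 1–4. Once the row is known, these 14 allocations carry no randomness of their own. The balance depends on how the table was filled.

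- *Digits drawn independently.* The number of even digits in a row is Binomial(10, ½). P(7:3 or worse) = 2 × (120 + 45 + 10 + 1)/1024 = 352/1024 = 34%. Over 24 families the intervention count is 3A + 2B, with A ~ Binomial(4, ½) for the positions used three times and B ~ Binomial(6, ½) for those used twice. Its variance is 9 × 1 + 4 × 1.5 = 15, SD 3.87, against √(24/4) = 2.45 with fresh digits. P(16:8 or worse) is 37%, against 15% with fresh digits.
- *Each row a permutation of 0–9.* Every row then has five even and five odd digits. Two passes give 10:10, and the last four families add between 0 and 4 to an arm, so the worst split is 14:10. The copying remains.

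**Scenario B: fresh independent digits for families 11–24.** The intervention count is Binomial(24, ½).
- P(12:12) = 16%.
- P(8:16 or worse) = 15% per cycle. P(at least one such cycle in five) = 1 − (1 − 0.152)^5 = 56%.
- Information relative to 1:1 is 4p(1 − p), with p the share in one arm. At 8:16 it is 4 × (1/3) × (2/3) = 0.889, a loss of 11% of that cycle's information.
- The average loss is 4 × Var(p) = 4 × 0.25/24 = 1/24, about 4% per cycle.
- Over all 120 families, P(48:72 or worse) = 3.5%, so about 96% of allocations are 49:71 or better. At 49:71 the loss is 1 − 4 × (49/120) × (71/120) = 3.4%.

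If rows are permutations and further rows are used, a cycle again cannot be worse than 14:10.

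**The case against.** The strongest reply is that this is a gap in a condensed article. Moving to the next row is ordinary use of a random-number table, the full protocol may say so, and the 24 per cycle is an estimate. There are also three centres. If a list were kept per centre, it would hold about 24/3 = 8 families, and one row would be enough.

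Part of this stands: the article may describe a sound procedure badly. But it sets out the procedure step by step, and those steps fail for any list longer than 10. No per-centre list is mentioned. The shortage of 100 digits against 120 families does assume that the single table described serves the whole trial.

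A reader might infer four stronger things that the article does not support.

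- *That the row was reused.* Nothing says so. The 34% figure also needs independently drawn digits.
- *That arm is confounded with cycle, centre or instructor.* With fresh digits this is simple randomization, which is unbiased. Chance imbalance costs precision only. Waitlist families receive no program before the posttest, so the control arm has no instructor to confound with.
- *That uneven cycles make child groups unworkable.* Groups of four to six can still be formed at 8:16 (4 + 4, and four groups of 4).
- *That concealment failed.* All outcome measures are completed at the screening interview, before assignment. Another team member telephones the result, and the interviewer is stated to be blinded to assignment. The unstated list order is a loose end and does not show a breach.

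**Conclusion.** The point holds as a contradiction between Study sample and Study design overview: the stated rule gives no allocation for 14 of 24 families in a cycle (58%), and the whole table cannot serve 120 families one digit each. This rests only on the figures in the article.

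The consequences are conditional. If a row was reused, those 14 families were not independently randomized, which would be serious whatever the resulting split. If fresh digits were drawn, the allocation is valid, and the cost is a modest loss of precision: 11% of a cycle's information at 8:16, and about 4% on average. The article does not let a reader tell which applies. It needs correcting because random allocation cannot be verified for most families. No bias has been shown.

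**What to change.** 1. For remaining cycles, replace the row rule with a pre-generated, concealed list of 24 allocations per cycle, 12 to each arm. A team member not involved in screening prepares it.
2. Fix and date the participant order, for example by screening number, before the list is opened. Allocate the whole cycle as one batch, so that a known 12:12 total does not make the last allocations predictable.
3. Include cycle as a factor in the analysis of covariance. With five cycles this uses four degrees of freedom.
4. For completed cycles, report how families 11–24 were allocated: row reused, further rows read, or another method. State whether the digits were drawn independently or permuted within rows, and give the split by cycle. If a row was reused, say so as a limitation.

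Stratification by centre is optional. The cost is a short script and a protocol amendment, with no extra staff or families.

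### As narrated, the digit row is read before the participant list is prepared, so allocation would not be concealed from whoever orders the list

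*Protocol article*

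**What the plan says.** The Study sample section of the protocol article sets out the randomization as a series of steps:

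1. "A 10 × 10 table was created by randomly assigning digits 0 to 9".
2. "One row of the table is randomly selected, and the sequence of digits in that row is observed".
3. "A participant list is prepared, and the sequence of participants is observed".
4. "The first digit will determine the first participant’s group, and so on".
5. "Participants with an even digit are assigned to the intervention group, and those with an odd digit are assigned to the control group".
6. "After the families are assigned to groups, another research team member contacts the parents by phone", to give the result and confirm participation.

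From the last step the article concludes: "It means that team member who interviews the families is blinded in the assignment process". It states no other safeguard.

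On what is known before allocation, the same section says: "During the screening interview, all outcome measures and demographic information are completed by the parents". The Methods/design section adds that the trial was expected to run in five cycles of 24 families, each cycle randomized between the two groups.

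**The concern.** The arm depends on two things only: the parity of the digit and the family's position on the list. Once the row has been read, the arm attached to every position is known. If the list is made after that, its order is the only part of the allocation still open, and it is in the hands of someone who may already know the digits. The article gives no ordering rule, such as study number or screening date, that would remove this discretion.

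The blinding sentence does not close the gap. It rests on a different person making the phone call once assignment is finished. Who reports the result afterwards says nothing about who ordered the list beforehand or what that person had seen.

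The arm comparison itself is at stake. Baseline scores exist before allocation, and families are handled in batches, so a whole batch could be arranged against known digits. The child-symptom, child-behavior and parenting-stress scales (SWAN, CBCL, PSI-SF) are completed by parents, and the comparator is a waitlist, so a parent's keenness could bear directly on the outcome. Keenness is not among the listed measures or baseline factors. Intention-to-treat analysis keeps families in the arm they were given, so it cannot repair a biased assignment. Analysis of covariance removes only the part of the selection that runs through the covariates used.

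**Working it through.** No figure in the article is at issue, so there is none to reproduce. The check is a reading of the steps, followed by one illustration of scale.

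**Reading the steps in the order given**

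| Step | What is then known | What is still open |
|---|---|---|
| Row selected and read | Parity, hence arm, of each position | Which family takes which position |
| List prepared | Family at each position | Nothing; arms follow by matching |
| Phone call by another member | Result given to the family | Nothing |

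The discretion lies in the second row of the table. The stated safeguard acts in the third and concerns the interviewer. Reversing the first two steps removes the problem, because a closed list leaves no positions to choose. A longer digit row would not remove it, so this is separate from whether a row holds enough digits for a cycle.

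**Scale, as an illustration only**

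Inputs:
- Families per cycle: 24 (Methods/design).
- Arm size per cycle: 12. This assumes an even split; allocation by parity does not guarantee one.
- Difference in expected outcome within an exchanged pair, d: 0.5 to 1 SD (assumed).
- Number of exchanged pairs, k: 1 or 2 (assumed).
- Planned effect: 0.6 (Estimation of sample size).

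Exchanging one pair raises one arm's mean by d/12 and lowers the other's by d/12. For k pairs the between-arm difference therefore shifts by 2kd/12:
- k = 1, d = 0.5: 2 × 1 × 0.5 / 12 = 0.083 SD
- k = 1, d = 1: 2 × 1 × 1 / 12 = 0.167 SD
- k = 2, d = 0.5: 2 × 2 × 0.5 / 12 = 0.167 SD
- k = 2, d = 1: 2 × 2 × 1 / 12 = 0.333 SD

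For the whole trial of 5 × 12 = 60 per arm, the result depends on how many cycles are affected:
- One exchange in one cycle only: 2d/60, or 0.017 to 0.033 SD.
- One exchange in every cycle, always in the same direction: 5 × 2d/60 = 2d/12, or 0.083 to 0.167 SD. Against 0.6 this is 0.083/0.6 = 14% to 0.167/0.6 = 28%.

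These shifts are before any covariate adjustment.

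**The case against.** The strongest objection is that the order of sentences need not be the order in time. Nothing such as 'then' or 'after' links reading the row to preparing the list. The two sentences are worded in parallel, and observing the participants' sequence may mean reading off an order that already existed. This stands: the article does not prove that the digits were seen first. But it introduces the passage as the procedure, gives the steps in this order, and says nothing to show that the list came first.

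A second objection is that ordering rules and staff roles are details a journal article may leave to the full protocol, which is not at hand. Silence alone would indeed be no finding. The point here is that the article does describe the steps, and the sequence it describes is weaker than the same steps reversed.

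Third, steering needs one person who knows both the digits and the families. The article does not say that the list-maker sees scores or judges motivation. A reader might infer that allocation is unconcealed from the whole team, or that families were steered. The document supports neither: it says the interviewer is blinded, and there is no evidence that any list was arranged. What stands is that concealment from the unnamed list-maker is not secured by the steps as written.

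Fourth, every input to the bias illustration other than the cycle size and the planned effect is assumed. Adjustment for baseline scores would remove much of any selection made on those scores. This is accepted. A reader might also want an inflated false-positive rate; none is offered, because it would further require an assumed frequency and direction of exchanges and an unadjusted test, whereas the article plans analysis of covariance.

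**Conclusion.** The concern holds conditionally. If the steps are carried out in the written order, allocation is not concealed from whoever prepares the list, and families already screened and scored could be placed with knowledge of their arm. The document shows opportunity, not occurrence. If the list was in fact fixed before the row was read, the concern largely resolves and the text only needs to say so.

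The shift of 0.08 to 0.17 SD in a cycle indicates what one exchange could do under the stated assumptions. It is not an estimate of bias in this trial. The matter deserves correction because selection at this step cannot be undone by intention-to-treat analysis, is only partly removed by covariate adjustment, and is almost free to prevent.

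**What to change.** For all remaining cycles:
- Complete consent, eligibility and baseline for the whole cycle. Then close and date the participant list in a fixed order, either study number or date of completed screening.
- Only after that, have an existing team member who took no part in screening or list preparation draw the digits and apply them.

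In the text:
- State the order of these steps and the role responsible for each.
- Reword the blinding sentence so that it claims only what the procedure delivers. A separate phone caller does not in itself conceal allocation from the person who orders the list.

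For cycles already allocated, state whether the list was fixed before the row was read, and disclose the cycles and number of families where it was not.

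The cost is negligible: the same digit table and staff, the steps reordered, and one paragraph of text. Past allocations cannot be redone, so for any affected cycle disclosure is the only remedy.

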## Methods/design

### Study design overview

The families of children with diagnoses of ADHD or with symptoms of inattention and hyperactivity are being recruited to participate in this study. The rationale for not restricting the study to children with formal diagnoses was that many children are first assessed by professionals after 6 in Hong Kong, and therefore many children with severe inattention and hyperactivity symptoms have not yet received a diagnosis.

A flowchart of the recruitment and implementation of this waitlist randomized controlled trial is illustrated in Fig. 1. All eligible families are randomized into a treatment group or a wait-list control group. The FBMI is delivered in a group format. All families in the waitlist control groups will undergo the same program after the posttest of the treatment groups. Three local non-government organizations in Hong Kong are participating in the study. The programs are conducted in the three collaborators’ district family service centers.

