### Statistical analysis

The baseline characteristics of the intervention group and the waitlist control group will be compared by analysis of covariance for continuous variables and chi-square tests for categorical variables. The baseline factors include the age of the children and the parents, the sex of the children and the parents, the children’s medication status, and the SWAN scores. The effects of FBMI will be tested by analysis of covariance, comparing the FBMI group (arm 1) to the wait-list control group (arm 2). All analyses will be carried out according to the intention-to-treat approach. The participants’ missing values will be imputed using the last-observation-carried-forward method. A two-sided *P* value of 0.05 or less will be considered be statistically significant.

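### Participation is re-confirmed in the same phone call that discloses the allocation, which invites arm-dependent withdrawal before the intervention starts

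*Protocol article*

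**What the plan says.** **The call.** The randomization paragraph under Study sample gives the order: "After the families are assigned to groups, another research team member contacts the parents by phone", and the purpose of that call is "to inform the parent about the results of randomization and to confirm that both the parent and the child will participate in the study".

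**What comes earlier.** Study design overview describes a screening interview at which a team member explains the procedure and design. It continues: "Once the parents agreed to participate in the study with their children, they were invited to sign on the consent forms before the study commenced". Study sample adds: "During the screening interview, all outcome measures and demographic information are completed by the parents". Study design overview also states: "All eligible families are randomized into a treatment group or a wait-list control group".

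**Attendance.** One exclusion criterion under Study sample is "the inability of either the parent or the child to attend 80 % of the program sessions".

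**Analysis.** Statistical analysis states: "All analyses will be carried out according to the intention-to-treat approach". Missing values are filled by last observation carried forward. The article does not say how a family that declines at the call is counted.

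**The concern.** A question about participation that is put after the arm is known can be answered differently in the two arms. A family drawn for FBMI must commit parent and child to sessions that are about to start. A wait-list family is asked about sessions that begin only after the treatment groups' posttest in an 8-week trial, or may withdraw because it has to wait. The reasons for declining, and so the kind of family lost, need not match.

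Parents know their arm, and the primary outcomes are parents' stress and the children's ADHD symptoms and behavior as rated by parents. A family's capacity to commit is plausibly related to its stress. If the more burdened FBMI families drop out at the call and are left out of the analysis while similar wait-list families stay, the treated arm looks better without any effect of the program. If the losses fall mainly on the wait-list side, the distortion can run the other way.

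**Working it through.** **1. Sequence.** Read together, the sections give: screening interview with explanation, agreement and baseline measures; eligibility; random assignment; phone call with disclosure and confirmation. Two links are not stated outright: that the consent form is signed before assignment, and what happens to a family that says no at the call. What is stated is that confirmation follows assignment and shares a call with disclosure.

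**2. Two ways to count a decliner who gives no posttest.**
- *Left out of the analysis.* The analyzed set is no longer the randomized set, contrary to the intention-to-treat statement.
- *Kept.* The only measurement on record is the one from the screening interview, so carrying the last observation forward makes it the outcome. If a share f of an arm declines and these families would have changed by g, that arm's mean is wrong by f × g. The article gives neither f nor g. This is a missing-data problem, not a loss from the denominator.

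**3. The plan's own figures.** The plan gives no refusal rate at the call; its 15% attrition is not split by stage or arm. The only plan figure used below as a yardstick is the effect size of 0.6. The sample size built on it, 45 per arm, is reproduced by a two-sided 5% t-test at 80% power (44.6, rounded up to 45). Then 45 / 0.85 = 52.9, so 53 per arm and 106 in total, as stated. The stated one-sided 5% would give 35.04, rounded up to 36. That mismatch is a separate matter and does not affect this point.

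**4. Illustration if decliners are left out.** The rates and gaps are assumptions, not document figures. With a share f declining in one arm only, and decliners worse than stayers by a gap D:

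shift in that arm's mean = f × D

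- f = 10%, D = 0.5 SD: 0.10 × 0.5 = 0.05 SD, and 0.05 / 0.6 = 8% of the planned effect.
- f = 20%, D = 0.5 SD: 0.20 × 0.5 = 0.10 SD, and 0.10 / 0.6 = 17%.

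**5. A second model as a check on scale.** Assume 60 per arm (120 families split equally), a share f lost from one arm only, and correlation ρ between the propensity to decline and a poor outcome. With z the normal quantile at f and φ the normal density:

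bias = ρ × φ(z) / (1 − f); SE = √(1/60 + 1/[60(1 − f)])

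| f | ρ | bias (SD) | share of 0.6 | actual type I error at nominal two-sided 5% |
|---|---|---|---|---|
| 5% | 0.2 | 0.022 | 4% | 5.2% |
| 10% | 0.3 | 0.058 | 10% | 6.1% |
| 15% | 0.3 | 0.082 | 14% | 7.2% |
| 20% | 0.5 | 0.175 | 29% | 14.7% |

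The last row in full: φ(z) = 0.280, so bias = 0.5 × 0.280 / 0.80 = 0.175. SE = √(1/60 + 1/48) = 0.194, so the test statistic is displaced by 0.175 / 0.194 = 0.90, and a nominal 5% test rejects about 14.7% of the time under no effect.

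Both models assume one-sided loss, exclusion of decliners and no baseline adjustment.

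**The case against.** The best reply is that the call is largely administrative. Agreement and the parent-completed measures belong to the screening interview, and only eligible families are randomized. A reader might infer from the call that families enter the trial only after learning their arm. The documents do not support that: what the call can affect is staying in the trial. This part of the reply stands.

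A reader might also infer that the 80% attendance criterion contradicts intention-to-treat. It does not. It is worded as expected inability, not as attendance achieved, and a criterion judged before assignment cannot depend on the arm. No section applies it after allocation or to actual attendance. The remaining risk is practical: a call that asks whether parent and child will take part could become a second availability check once the dates are known.

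On size, the reply is right that every rate in the illustration is assumed, that wait-list families may refuse too and so shrink or reverse the bias, and that analysis of covariance with baseline scores would absorb part of a prognosis gap. It would not absorb motivation or capacity that the baseline scores miss. A shift of 0.05 to 0.10 SD is also below one standard error of the comparison, √(2/60) = 0.18 SD at 60 per arm. But a systematic shift is not averaged out by chance, and this one is avoidable.

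Finally, a family may decline the sessions and still give a posttest, and the detailed rule for the analysis set may stand in a fuller document. Both are fair. Neither changes the order of steps, which the article itself fixes.

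**Conclusion.** The point holds in a limited form. The plan puts a confirmation of participation after disclosure of the arm, which opens a route to arm-dependent withdrawal before the intervention. The intention-to-treat statement and carrying the last observation forward do not close it: the first is broken if decliners are not counted, and the second substitutes the screening value if they are counted but not followed.

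The documents do not show that any family will decline or be dropped, so neither the size nor the direction of a bias can be derived from them. The range of 0.05 to 0.10 SD (8% to 17% of the planned 0.6) holds only if 10% to 20% of one arm and none of the other refuse, decliners are 0.5 SD worse than stayers, and decliners are left out of the analysis. The second model, with its own assumptions, spans 0.02 to 0.175 SD. Baseline adjustment would reduce either figure.

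**What to change.** - At the screening interview, before assignment: complete consent, confirm that parent and child are available for both the immediate and the delayed program dates, and judge the 80% criterion. State this order in the text.
- Limit the call after allocation to notification. It can still be made by a different team member, so the interviewer's blinding is unaffected.
- State that every family whose allocation was drawn is analyzed in its assigned arm, and seek the posttest from all of them whatever they say at the call.
- Report refusals at the call by arm.

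The cost is one reordered contact and a few sentences on the analysis set and the flow diagram. A few families that cannot meet both sets of dates may be screened out earlier. Seeking posttests from families that decline the sessions takes some extra follow-up work.
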